**Figure 1 F1:**
[figure not shown]
Baseline and follow-up assessment.

The 75% randomly selected patients without depression and/or anxiety provides a higher number of patients in the observation group 3 (P−/−) than the power calculation suggests (see section *Sample size calculation*). The higher number is chosen for quality assurance. A group of patients without depression and anxiety which is too small would reveal the focus on depression and anxiety in this study. Therefore the proportion of patients with depression and/or anxiety and without depression/anxiety will be 1:3 in each interview.

Symptoms of anxiety and depression are addressed within a full list of somatic comorbidities, introduced by the somatic conditions of the Charlson Comorbidity Index [46] and followed by a question concerning any further comorbidity, which has not been addressed in the list before. The focus on depression and anxiety within this study is not revealed to the GPs. During the interview the GPs have full access to all patient data within their electronic records. The recognition of depression and/or anxiety is operationalized as the GP’s judgement in the telephone interview as to whether or not the patient displays symptoms of depression and/or anxiety. If the GP states that the patient displays symptoms, the GP is asked if he or she judges this as a clinical diagnosis or if he or she considers the symptoms not severe enough for a diagnosis.

In a next step, patient information from the questionnaire and GP judgment regarding depression and anxiety are matched and the patients are allocated to one of the following groups:

● Observation group 1 (P +/+): All patients with depression and/or anxiety whose depression and/or anxiety has been recognized by the GP

● Observation group 2 (P +/−): All patients with depression and/or anxiety whose depression and/or anxiety has not been recognized by the GP

● Observation group 3: P (−/−) Sample of patients without depression and anxiety who were randomly selected for telephone interview. In the interview the GPs did not diagnosed any depression or anxiety.

Patients without depression and anxiety whose GP nevertheless diagnosed depression or anxiety P(−/+) will be considered separately.

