### Study endpoints

The primary outcome of this longitudinal study is the quality of life after 12-months of follow-up. The secondary outcome is the prognosis of heart failure in terms of hospital admissions and mortality risk within the 12-month follow-up period. Group comparisons will contrast patients with depression and/or anxiety recognized by the GP (observation group 1: P(+/+)), patients with depression and/or anxiety not recognized by the GP (observation group 2: P(+/−)) and patients without depression and/or anxiety whose GPs did not diagnose any depression or anxiety (observation group 3: P(−/−)). For further information see Table 1.

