### Data collection

Data is collected at the baseline assessment and at the follow-up assessment 12 months later. In the baseline assessment the patient receives a self-administered questionnaire by mail (see Table 2), as well as a free return envelope. Five days after the questionnaire is sent the patients receive a reminder by mail. Based on the information provided in the questionnaire, the patients are assigned to one of three observation groups. For more details see section *Recognition of depression and anxiety*. The GP of each patient assigned to one of the observation groups is interviewed by study staff in a telephone-interview. During the interview the GP has access to all patient data in his or her medical records. The questions regarding depression and anxiety are collected along with a comprehensive list of further comorbidities (see Table 2).

**Table 2 T2:** Data collection

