**GPs: Telephone-interview with insight in the medical record**	
Validation of heart-failure diagnosis	Does the patient have heart failure?/Severity level according to New York Heart Association (NYHA) class/Ejection fraction
Size of practice	Number of GPs in the practice/ Practice type (single practice/practice sharing/group practice)/Number of patients insured by the statutory health insurance per quarter/ Percentage of private patients
Familiarity with the patient	Are you the regular GP of the patient?/How well do you know the patient? (Scale 1 to 10)
Comorbidity	Charlson Comorbidity Index [46]/Which additional diseases does the patient have?
Depression/Anxiety	Does the patient have any symptomatology of depression/anxiety? If yes, please specify/Had the patient any symptomatology of depression/anxiety in the past?
Measures taken if depression/anxiety is recognized	What treatment have you prompted?
Treatment of heart failure	What difficulties have you encountered when treating the heart failure in this patient? Have there been any reasons to deviate from the recommended pharmacological treatment?
Sociodemographic data of the GP	Age/Gender/Years of practice/Speciality/Additional trainings

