In the main study, the case finding algorithm (identified in the SCID sub-study) is applied on the information given in the baseline questionnaire. Therefore, the questionnaire includes the same self-administered instruments as used in the sub-study (HADS, PHQ-9 and GAD-7, PROMIS Depression and Anxiety scales). Depending on the algorithm from the sub-study, the patients are classified as patients with depression and/or anxiety or patients without depression and/or anxiety. Due to the work load, we do not interview the GPs of 25% of the patients without depression and anxiety by phone. Therefore, for each practice 75% of all patients without depression and/or anxiety (group P-) are randomly selected for telephone interviews with the GP and assigned to the observation group 3 (P-).

After baseline assessment, GP interviews will be available for each patient assigned to one of the three observation groups. For further detail see Figure 1.

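### GP recognition is judged at an interview held after the questionnaire, and the 12-month period for admissions and deaths is not tied to that interview, so an admission in between could both create recognition and count as outcome

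*Protocol article*

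**What the plan says.** The two halves of the exposure are fixed at different moments.

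- **Patient status.** Under Recognition of depression and anxiety, "the case finding algorithm (identified in the SCID sub-study) is applied on the information given in the baseline questionnaire". Data collection agrees: "Based on the information provided in the questionnaire, the patients are assigned to one of three observation groups".
- **Order of steps.** Data collection then states: "The GP of each patient assigned to one of the observation groups is interviewed by study staff in a telephone-interview". Before the calls, "for each practice 75% of all patients without depression and/or anxiety (group P-) are randomly selected for telephone interviews", so scoring and a draw come first.
- **Recognition.** It is defined as the GP's "judgement in the telephone interview as to whether or not the patient displays symptoms of depression and/or anxiety". The Table 2 item is in the present tense: "Does the patient have any symptomatology of depression/anxiety". A second item asks "Had the patient any symptomatology of depression/anxiety in the past", with no date. The GP has the complete electronic record available during the call.
- **Outcome period.** Study endpoints sets the secondary outcome as "hospital admissions and mortality risk within the 12-month follow-up period". Data collection places follow-up 12 months after the baseline assessment. The Table 2 follow-up items ask about admissions and deaths over the preceding 12 months, with dates.
- **Use.** The second step of Data analysis compares P+/+ with P+/− on quality of life, hospitalisation and mortality. Chi-squared tests, Kaplan-Meier curves, Cox regression and a regression of hospital days are planned.

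**The concern.** An exposure should be settled before the period in which its outcomes are counted. Here a patient who is unrecognised on returning the questionnaire may be admitted before the GP is called. A discharge letter or a visit after discharge may then bring the mood problem to the GP's notice. At the interview the patient is recognised and enters P+/+. If the 12 months run from the questionnaire, the same admission is also an outcome event in P+/+. Admissions are thereby moved out of P+/− and into P+/+, and recognition looks harmful even if it has no effect.

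Adjustment for comorbidity, sociodemographics and heart failure severity does not cure this, because the exposure is partly defined by the outcome. A patient who dies between questionnaire and interview also has no natural answer to a present-tense question about symptoms.

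At stake are the secondary comparisons of admission and mortality between recognised and unrecognised patients.

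**Working it through.** **1. The plan's own figures.** Sample size calculation gives 504 recognised and 168 unrecognised patients for 5 EQ-VAS points, 80% power and α = 0.05. With an assumed SD of 20 (none is stated), two-sided, the smaller group needs (1.960 + 0.842)² × 20² × (1 + 1/3) / 5² = 167.4, so 168, and 3 × 168 = 504. The figure reproduces. It says nothing about timing, but it supplies the 75% recognition rate and the group sizes used below.

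**2. A null model for the gap.** Recognition has no effect, and recognition at the questionnaire is independent of admission.

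- R = 12-month admission risk: 40%, an assumption.
- r = recognition at the questionnaire: 75% (Sample size calculation). The alternative is 42.5%, which the Background cites from a study of ambulatory heart failure patients.
- L = gap in months: 0.5 to 3, an assumption.
- c = probability that an admission in the gap turns an unrecognised patient into a recognised one: 0.10 to 0.50, an assumption.
- The admission hazard is constant and the clock starts at the questionnaire.

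Formulas:

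- q = 1 − (1 − R)^(L/12), the risk of an admission in the gap
- recognised share = r + (1 − r)·q·c
- admission risk in P+/+ = [r·R + (1 − r)·q·c] / recognised share
- admission risk in P+/− = (1 − r)·(R − q·c) / (1 − recognised share)

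Worked case, L = 3, c = 0.50, r = 0.75:

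- q = 1 − 0.6^0.25 = 0.120
- recognised share = 0.75 + 0.25 × 0.120 × 0.50 = 0.765
- P+/+ = (0.300 + 0.015) / 0.765 = 0.412
- P+/− = 0.25 × (0.40 − 0.060) / 0.235 = 0.362
- difference 5.0 points, risk ratio 1.14

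**3. False risk ratio, P+/+ v P+/−, R = 40%**

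| Gap | q | r = 75%: c = 0.10 / 0.25 / 0.50 | r = 42.5%: c = 0.10 / 0.25 / 0.50 |
|---|---|---|---|
| 2 weeks (0.5 month) | 0.021 | 1.004 / 1.011 / 1.022 | 1.007 / 1.019 / 1.038 |
| 1 month | 0.042 | 1.008 / 1.021 / 1.044 | 1.015 / 1.037 / 1.075 |
| 2 months | 0.082 | 1.017 / 1.043 / 1.090 | 1.029 / 1.074 / 1.152 |
| 3 months | 0.120 | 1.025 / 1.064 / 1.138 | 1.043 / 1.110 / 1.230 |

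With 672 patients and r = 75%, the chance of a significant result against recognition, nominally 2.5%, is 2.7% to 3.8% at two weeks and 4.1% to 19.8% at three months.

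**4. After the change.** If only admissions from the interview onward are counted, the risk after the interview does not depend on whether an earlier admission prompted recognition. The false risk ratio in this model is 1.00. That relies on one hazard shared by all patients. If sicker patients are admitted both before and after the interview, ordinary confounding remains, but the double counting is gone.

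**The case against.** The strongest reply is that the clock may already start at the interview. The Abstract says GPs are interviewed at baseline, Table 2 lists the interview under baseline, and follow-up is 12 months after the baseline assessment. Figure 1 is not shown and may give the timing. An interview window is the kind of detail an article leaves to the full protocol, so its absence is no finding. This stands in part: the double counting is conditional. The definition of recognition, however, is stated, and it is anchored to the interview. A short window would shrink the problem without correcting the definition.

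Second, the gap may be short. Some delay is built in, but sampling within practices is compatible with rolling batches, and at two weeks the bias is negligible. Even the 5.0-point difference is close to one standard error of the comparison: √[0.40 × 0.60 × (1/504 + 1/168)] = 4.4 points. This stands and limits the weight of the point.

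Third, dating only the depression/anxiety answer against the questionnaire would single that item out and could weaken the masking described under Quality assurance. This stands and shapes the fix.

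Some stronger readings are tempting, but the article does not support them:

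- **GP contacts in the gap also count as outcome.** The contact item looks back six months only, so at 12 months it would miss them unless the gap exceeded about six months. Contacts are the subject of a research question and are not an endpoint.
- **Patients who die in the gap are scored as unrecognised.** Nothing says so; their handling is simply not described.
- **The primary outcome is double counted.** Quality of life at 12 months is a point measure. Events in the gap could still affect who is classified as recognised.
- **The bias is certainly large.** Raising recognition from 75% to 90% after an admission means that (0.90 − 0.75)/0.25 = 60% of unrecognised patients convert. With 30% to 40% admitted and a 12-week gap, that yields risk ratios of 1.16 to 1.17. The arithmetic is right, but nothing in the article supports so high a conversion.

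**Conclusion.** The point holds for the secondary outcomes, conditionally. Patient status and recognition are taken at different times, recognition can draw on records made after the questionnaire, and the outcome period is not tied to the interview. If that period runs from the questionnaire, which is the natural reading of a 12-month look-back but is not stated, admissions in the gap can enter both exposure and outcome and make recognition look harmful.

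The size is unknown. It is negligible at about two weeks. At three months the false risk ratio reaches 1.14 with 75% recognition, or 1.23 with the 42.5% rate the article also cites. These figures assume 40% admission and at most 50% conversion. A reader might infer that the recognised v unrecognised comparison is biased outright; the article supports only that it is open to this bias. The point is worth acting on because the repair is cheap.

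**What to change.** - For the P+/+ v P+/− comparisons of admission and mortality (chi-squared tests, Kaplan-Meier, Cox and hospital days), define time zero as the date of the GP interview.
- Exclude admissions before that date, using the admission dates already collected at follow-up.
- Report deaths before the interview separately, as patients whose recognition cannot be classified.
- Optional: ask the GP for the first date in the record for every listed comorbidity, so that depression and anxiety do not stand out. Use recognition recorded on or before the questionnaire date as a sensitivity analysis.

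**Cost.** The main change is a few lines in the analysis section. It needs only that each interview date is kept. The sample size, which is set on EQ-VAS, and the masking are unaffected. The few admissions in the gap are lost to these comparisons. If the follow-up call is timed from the questionnaire, time at risk is 12 months minus the gap, so the binary comparisons need one common horizon from the interview. The optional dating lengthens each call.

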### Sample size calculation

Given a prevalence of psychosocial risk factors (depression, anxiety or both) in HF patients from general practices of 20% [6] and a recognition rate of 75% [20], we aim for a sample that provides us a minimum power of 80% to detect a minimum difference of at least any 5 points on the EQ-5D visual analogue scale (EQ-VAS) [42] with α = 0.05. Therefore, a sample of 672 participants with depression and/or anxiety is needed, of whom 504 have depression and/or anxiety recognized by their GP (P+/+) and 168 with depression and/or anxiety not recognized by their GP (P+/−).

Given an estimated participation rate of 40%, a return rate of the baseline questionnaire of 90% and a loss to follow-up rate of 15% a total of 10,973 patients with heart failure are needed to be invited into the study by their GP (see Figure 2).

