**Figure 2 F2:**
[figure not shown]
Sample size considerations.

For a comparison with heart failure patients without psychosocial risk factors, a random sample of N = 2,370 of those who completed the baseline questionnaire but were not identified to have depression and/or anxiety will be drawn (P−/−). Taking a loss to follow-up rate of 15% into account, a total of 2,015 patients with heart failure but without depression and/or anxiety at baseline will be included in the analyses. A minimum number of 118 patients at the follow-up assessment would already provide a power of 80% to detect differences between the groups (P+/+, P+/− and P−/−) of at least any 5 points on the EQ-5D visual analogue scale (EQ-VAS) [42] with α = 0.05.

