### Data analysis

The prevalence of comorbidities in patients with HF and difficulties in the treatment of patients with HF will be analyzed by descriptive statistics. The prevalence of recognition/non-recognition of psychosocial risk factors in primary care HF patients and its impact on the study endpoints will be analysed. In a first step we will compare quality of life, hospitalisation and mortality after a 1-year follow-up period between HF patients with depression/anxiety (P+/+ and P+/−) and those without (P−/−).

In the second step we will compare quality of life, hospitalisation and mortality after a 1-year follow-up period between HF patients with depression and/or anxiety recognized by their GP (P+/+) and those with depression and/or anxiety not recognized (P+/−). We will perform multivariate regression models taking the confounding effects (e.g. comorbidity, sociodemographics, type of treatment for depression/anxiety and heart failure severity) into account.

In a third step we will compare several types of treatment for psychosocial risk factors and their potential effects on quality of life, hospitalisation and mortality after a 1-year follow-up period.

We will compare the information concerning the treatment of psychosocial risk factors gathered from patients with that gathered from GPs to evaluate potential differences (e.g. due to treatment initiated by other healthcare providers than the GP). We will re-run the analyses of the third step for information gathered from patients and for information gathered from GPs separately.

For binary outcomes (hospitalization, survival after 1 year), chi-squared tests will be used. For continuous outcomes (quality of life, survival time), t-tests or non-parametric rank tests will be used. Multivariate linear regression analyses will be performed for the total number of hospitalized days, Cox regression and Kaplan-Meier curves for time to hospitalization survival time. Multivariate linear regression will be used for quality of life.

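### Step 1 sets all questionnaire-positive patients against only those questionnaire-negative patients whom the GP also calls negative, and the counts labelled P−/− are counts of all interviewed P−

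*Protocol article*

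**What the plan says.** All references are to the protocol article.

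- **Research questions (Methods/Design).** One question asks whether the presence of depression or anxiety is associated with quality of life and prognosis. A separate one asks about recognition by the GP.
- **Recognition of depression and anxiety (Methods/Design).** P+ and P− are set by the questionnaire algorithm. A random 75% of P− patients in each practice is drawn for GP interview, and the whole draw is assigned to group 3 before any interview. After the interviews, group 3 is narrowed to those in whom the GP found no depression or anxiety, and "Patients without depression and anxiety whose GP nevertheless diagnosed depression or anxiety P(−/+) will be considered separately".
- **Same section, GP criterion.** Recognition is defined as the GP's "judgement in the telephone interview as to whether or not the patient displays symptoms of depression and/or anxiety". A follow-up question separates a clinical diagnosis from symptoms too mild for one.
- **Study endpoints.** Group 3 is questionnaire-negative and also without a GP diagnosis.
- **Table 1.** No explicit GP condition is set for group 3.
- **Sample size calculation.** The comparator is a "random sample of N = 2,370 of those who completed the baseline questionnaire but were not identified to have depression and/or anxiety", labelled P−/−. Then: "Taking a loss to follow-up rate of 15% into account, a total of 2,015 patients".
- **Data analysis, step 1.** The comparison is "between HF patients with depression/anxiety (P+/+ and P+/−) and those without (P", and the closing bracket names P−/−.

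**The concern.** Step 1 is the only listed step that can answer the presence question. Its two arms are selected by different rules. A P+ patient stays in whether or not the GP agrees, while a P− patient stays in only if the GP agrees. The comparator therefore depends on GP judgement, which the article treats elsewhere as a separate question. A difference found in step 1 could not be attributed to presence alone.

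The text also supports two versions of group 3: all interviewed P−, or only those with a negative GP judgement. Two analysts could build different comparators from it. The expected counts fit the first version but carry the label of the second.

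A smaller wording matter adds to this. The article defines recognition by symptoms, but describes the split of P− patients with the word diagnosed.

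**Working it through.** **1. Reproducing the plan's counts.** Inputs from Sample size calculation: 10,973 invited, 40% participation, 90% questionnaire return, 20% prevalence, 15% loss to follow-up. The 75% sampling fraction comes from Recognition of depression and anxiety.

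- Questionnaires returned: 10,973 × 0.40 × 0.90 = 3,950
- P+: 3,950 × 0.20 = 790. At follow-up 790 × 0.85 = 671.5 (stated 672)
- P−: 3,950 × 0.80 = 3,160
- Drawn for interview: 3,160 × 0.75 = 2,370 (stated 2,370)
- At follow-up: 2,370 × 0.85 = 2,014.5 (stated 2,015)

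Every stated figure is reproduced with no term for P−/+. The ratio 2,370 / 790 = 3 also matches the 1:3 mix planned for each interview. So 2,370 and 2,015 count all interviewed P−, that is P−/− plus P−/+.

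**2. P−/− after removing P−/+.** The P−/+ share f is not given, so a range is assumed, with equal loss to follow-up in both cells. Baseline = 2,370 × (1 − f); follow-up = baseline × 0.85.

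| f (assumed) | P−/− at baseline | P−/− at follow-up |
|---|---|---|
| 5% | 2,252 | 1,914 |
| 10% | 2,133 | 1,813 |
| 20% | 1,896 | 1,612 |
| 30% | 1,659 | 1,410 |

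At f = 10% about 201 patients (0.10 × 2,014.5) leave the comparator at follow-up, more than the 168 planned for P+/−.

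**3. Shift in the step 1 comparator.** Let m be the mean 12-month EQ-VAS in P−/− and m − d the mean in P−/+. The mean over all P− is (1 − f)m + f(m − d) = m − f × d. Using P−/− alone therefore raises the comparator mean by f × d.

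| f | d = 5 | d = 10 | d = 15 |
|---|---|---|---|
| 5% | 0.25 | 0.50 | 0.75 |
| 10% | 0.50 | 1.00 | 1.50 |
| 20% | 1.00 | 2.00 | 3.00 |
| 30% | 1.50 | 3.00 | 4.50 |

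These compare with the 5-point EQ-VAS difference in Sample size calculation. Both f and d are assumptions, including the sign of d.

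**4. Power.** The SD is not stated. With a two-sided α of 0.05 and a 3:1 allocation, SD 20 gives (1 + 1/3) × [20 × (1.960 + 0.842) / 5]² = 1.333 × 125.6 = 167.4, rounded up to 168. This is the plan's P+/− count, so SD 20 is inferred. With it, power to detect 5 points is:

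- against 672 P+: above 99.9% for f from 0 to 30%;
- against 168 P+/−: 87.6% at f = 0 and 86.5% at f = 30%.

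On the plan's own minimum of 118, the loss would have to reach 1 − 118/2,015 = 94% before it mattered.

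**The case against.** **A stated choice.** Study endpoints and the recognition section both describe group 3 as negative on questionnaire and GP judgement, and Data analysis uses P−/− accordingly. Concordant negatives are a legitimate reference group, and how P−/+ are analysed separately can be left to the full plan. This stands as far as the separate analysis goes. It does not remove the mismatch between the stated step 1 contrast and the presence question, or the conflict over who belongs to group 3.

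**Inflation is not shown.** A reader might infer that step 1 exaggerates the association. The documents do not support this. P−/+ patients may be remitted or treated cases, whose removal makes the comparator healthier than P− as a whole. They may equally be cases that the self-rating scales missed, whose removal reduces misclassification. Nothing in the article says which type dominates. This objection stands.

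**The GP criterion.** A reader might infer a fixed rule under which the same GP answer, symptoms too mild for a diagnosis, counts as positive for a P+ patient and negative for a P− patient. That rests on one verb. The article defines recognition once, by symptoms, and then says GP judgement is matched for all groups, so diagnosed may be loose wording. It needs aligning; it is not shown to be a second criterion.

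**Recognition judged only in the still symptomatic.** This might be read as a flaw, but the research question concerns depression or anxiety that is present, so the restriction is intended.

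**Only a label.** The text describes the 2,015 as patients without depression or anxiety at baseline, which is true of questionnaire-negative patients, and the number is deliberately larger than power requires. For power, this stands. The P−/− label is still wrong, because the article itself expects some P−/+.

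**Conclusion.** The point holds in a limited form. As written, step 1 does not isolate the presence of depression or anxiety, because its comparator is also selected on GP judgement while its case group is not. The comparator mean moves by f × d: 0.25–4.5 points for assumed f of 5–30% and d of 5–15 points. The documents give neither quantity, and whether the net effect is a bias upwards or downwards is open.

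Group 3 is defined in two ways. The 2,370 and 2,015 are P− counts, and 2,015 analysed P−/− patients can be reached only if there are no P−/+ patients at all.

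This is not a power problem, given the inferred SD of 20, and it does not touch step 2 (P+/+ against P+/−). It should be corrected, since the remedy needs no new data.

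**What to change.** - Define group 3 one way in Table 1, Study endpoints, the recognition section and Sample size calculation.
- In step 1, compare all P+ with all interviewed P− (P−/− plus P−/+), and report the P−/− comparator alongside it. The interviewed P− are a random draw within each practice, so they represent P− as a whole.
- Replace the word diagnosed in the group definitions with the symptom judgement that the article defines as recognition, so that one GP criterion applies to all four cells.
- Relabel 2,370 and 2,015 as P−, and state that P−/− will be smaller by the P−/+ share.

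The cost is wording, two relabelled counts and one additional analysis. Both GP answers and the follow-up data for these patients are already part of the planned data collection.
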